### Sample size

The primary outcome of the study is defined as the proportion of mother-newborn retained in PMTCT care at 24 months; assuming i) a power of 80 %, ii) a two-sided test (alpha = 0.05), iii) and based on prior knowledge, a proportion retained in the control group of about 30 %, a sample size of 300 participants in each arm for a total of 600 subjects, with 5 % dropout rate (i.e. women who decide to withdraw from the study) in both the control and intervention arms was estimated to detect a 11 % difference (the smallest detectable difference) in the primary outcome between the intervention and control arms that is the difference that it would be important to detect is 11 %, computed as the proportion retained in the intervention arm minus the proportion retained in the control arm i.e. the proportion retained in the intervention group minus the proportion retained in the control group. Calculations were performed using Stata 14.1.

### Recruitment

A PMTCT nurse at the selected clinics will inform all consecutive pregnant women identified as living with HIV at their first ANC visit about the study. The PMTCT nurse will then refer these clients to the research assistant who will assess their eligibility and provide detailed information about the study. Individuals who are eligible will be invited to participate in the study and the research assistant will seek their consent.

Participants in the intervention arm who own or have access to mobile phones will be registered directly onto the WelTel platform with their phone number.

### Randomization and allocation

Eligible and consenting patients will be randomized to the intervention and control arms using a 1:1 allocation ratio. To ensure balance between the arms throughout the trial, we adopted a permuted-block randomization scheme. The block size will be concealed until the trial is over. Randomization will be performed separately at each clinic. We will use opaque sealed envelopes to assign participants to the intervention and control arms. The randomization list was be generated at the Karolinska Institutet (Stockholm, Sweden) by an independent statistician.

### Baseline

An interviewer- facilitated baseline questionnaire will be administered after recruitment and allocation. Questions record information on participants’ social and demographic characteristics; time of HIV diagnosis, time on ARV, disclosure of HIV status, HIV care and social support, mobile phone use as well as costs for accessing care.

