## Methods/design

### Trial design

The WelTel PMCT study is a 4–7 center two-arm open randomized controlled trial in which the intervention is allocated in a 1:1 ratio (Fig. 1 trial design).

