### Study population

The study population will consist of: (i) pregnant women living with HIV aged 18 and over presenting at ANC for a first visit in the current pregnancy at the selected clinics; and (ii) newborns delivered to these women living with HIV. Women who will be pregnant and will be diagnosed with HIV infection will be referred to a male or female research assistant to complete a checklist for eligibility. Determination of HIV infection will be based on two repeated Determine or Colloidal Gold tests for women newly diagnosed during the current pregnancy, or, based on referral from the comprehensive care clinic for those with known HIV infection and on antiretroviral therapy (ART) or pre-ART). Individuals must fulfill all the inclusion criteria, provide consent to participate and complete an interviewer-administered questionnaire before they are randomized to either the control and intervention groups.

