### Data collection and management

All outgoing and incoming text messages will be automatically recorded on the WelTel platform. The platform also captures all of the “problems” noted by participants, instances of non-response, and actions taken in relation to participants’ ‘problem’ responses and non-responses. Platform data will be backed up every 7 days.

All questionnaires will be paper-based and the data manager will then enter data into a database at the central office on an ongoing basis. A data manager will check the forms for completeness and quality will be verified by re-checking a random sample of 10 % of the data. Any problems that arise will be resolved promptly. Participant files will be stored in a locked office at the trial sites.

Data on attendance, HIV care clinical indicators like viral load and CD4 cell count as well as treatment regimen will be collected medical records. We will also collect information on demographic characteristics (age, education level, marital status and parity) of all screened patients/potential trial participants.

Qualitative research using in –depth interviews will also be performed to discover ‘how’ and ‘why’ the intervention works to improve retention in PMTCT program. Purposive sampling will be used to identify participants for qualitative interviews. Face-to-face interactions will be used to build trust during the interview process and to enhance free interaction between the researcher and the participants [20]. All conversations will be recorded with permission from the respondents and the interviews will be performed at a place and in a language preferred by the respondent.

All qualitative research tools will be developed in English, then translated to Kiswahili, and then back translated to English. The interview guide will be available in both languages.

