For the primary outcome, we will compare the proportion of mothers living with HIV and their HIV-exposed infants in the program at 24 months post-birth in the intervention vs. control arm using both parametric (Chi-Square) and exact (Fisher) statistical tests. Secondary outcomes will also be compared between arms, with t-tests for normally distributed variables, Mann Whitney-U tests for non-normally distributed variables, and Chi-Square and Fisher exact tests for categorical variables. The relative risk (RR) for PMTCT retention with 95 % confidence intervals will be computed and the number needed to treat to prevent one non-retained mother-infant pair will also be estimated. Concerning the secondary outcomes, average treatment effects (ATE) will be computed for continuous outcomes and RRs for categorical outcomes. For both primary and secondary outcomes, log-linear or linear regression models will be used to provide effect estimates adjusted for potential imbalances in baseline participants’ characteristics, if required. We will repeat the analysis of primary and secondary outcomes within such subgroups (in relation to socio-demographics) to assess the homogeneity of the intervention effect across pre-determined subgroups of patients. Stratified RRs and ATEs will be computed. Regression models, which include the intervention allocation and subgroup-defining variables and their interaction, will be applied to assess effect modification across groups; all statistics tests will be run based on two side *p*-values and values <0.05 will be considered statistically significant. All statistical analyses will be again performed with Stata version 14.1 (Stata Corporation, College Station, TX, USA).

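### The protocol places the baseline questionnaire both before randomisation and after allocation; in an open trial the second order would make some self-reported baseline covariates post-randomisation data

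*Protocol article*

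**What the plan says.** Under Study population, meeting the inclusion criteria and consenting are not enough for randomisation. A woman must also "complete an interviewer-administered questionnaire before they are randomized to either the control and intervention groups". Under Baseline, the order is the opposite: the "baseline questionnaire will be administered after recruitment and allocation". Its content includes "disclosure of HIV status, HIV care and social support, mobile phone use as well as costs for accessing care". The section on randomisation and allocation mentions no questionnaire, so it does not settle the order.

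Trial design describes a "two-arm open randomized controlled trial in which the intervention is allocated in a 1:1 ratio". Statistical methods lists the baseline characteristics to be reported by arm, with HIV status disclosure and phone ownership among them. It also plans regression models, where needed, that give "effect estimates adjusted for potential imbalances in baseline" characteristics, and subgroup analyses on socio-demographic variables: "Regression models, which include the intervention allocation and subgroup-defining variables and their interaction, will be applied to assess effect modification".

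Under Data collection and management there is a separate source: "We will also collect information on demographic characteristics (age, education level, marital status and parity) of all screened patients/potential trial participants". Attendance, clinical indicators and treatment regimen come from medical records.

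**The concern.** A site cannot follow both orders. If it follows the Baseline section, the woman knows her arm when she answers, and nothing in the article keeps it from the interviewer. Being offered a weekly text exchange about HIV care, possibly on a shared phone, could change what she says about disclosure or about her phone. A difference between arms in those answers would then look like a chance imbalance when it is a reporting effect. It is also the kind of difference that would prompt the optional adjustment, and adjusting for it would move an estimate that needed no correction.

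There is a second, smaller route. A woman who leaves after learning her arm but before the interview would lack the covariates found only in the questionnaire. She would fall out of any model that uses them, and such losses could differ by arm.

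**Working it through.** **Is it one questionnaire or two?** Study population does not use the word baseline for its questionnaire, so a separate form is conceivable. However, it names the eligibility checklist separately, and the only participant questionnaires the article describes are the baseline and follow-up ones. Follow-up cannot precede randomisation, so the baseline questionnaire is the natural reading. Even if a different form were meant, the Baseline section alone would still put baseline collection after open allocation.

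**Which items are exposed?** Setting the Baseline content against the list in Statistical methods:

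- In both and open to influence: HIV status disclosure; more weakly, phone ownership.
- Asked but not on the list: social support and costs of access.
- On the list but hard for knowledge of the arm to change: age, parity, marital status, education, distance, number of children, time since diagnosis, ARV status and duration.

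**Which analyses use them?** The baseline table does. The adjusted models and subgroups may. The chi-square and Fisher tests, the unadjusted relative risk and the number needed to treat do not.

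**Illustration of size.** The protocol has no figure of its own to reproduce here. All inputs below are assumptions; only the 11-point target (Sample size) comes from the protocol.

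- True disclosure D is 50% in both arms, and the true treatment effect is zero.
- Disclosed women have retention higher by g = 0.20 or 0.30.
- Control women report truthfully. In the SMS arm reported disclosure R is 50% plus a shift s of 5 or 10 points, because 10% or 20% of non-disclosed women report disclosure, unrelated to their retention.

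For a linear model of retention Y on arm and R with equal arms, the adjusted effect is

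(difference in mean Y) - b × (difference in mean R) = 0 - b × s,

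where b = [Cov(Y,R) in SMS + Cov(Y,R) in control] / [Var(R) in SMS + Var(R) in control].

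Control arm: Cov = 0.25g, Var = 0.25.

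SMS arm, s = 0.10: Var = 0.60 × 0.40 = 0.24; Cov = g(0.50 - 0.50 × 0.60) = 0.20g. So b = 0.45g/0.49 = 0.918g.

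SMS arm, s = 0.05: Var = 0.55 × 0.45 = 0.2475; Cov = g(0.50 - 0.50 × 0.55) = 0.225g. So b = 0.475g/0.4975 = 0.955g.

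| Shift s | g = 0.20 | g = 0.30 |
|---|---|---|
| 10 points | -0.10 × 0.918 × 0.20 = -1.8 points | -0.10 × 0.918 × 0.30 = -2.8 points |
| 5 points | -0.05 × 0.955 × 0.20 = -1.0 points | -0.05 × 0.955 × 0.30 = -1.4 points |
| 0 | 0 | 0 |

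The unadjusted difference is zero in every cell, as it should be. If instead 10% or 20% of disclosed SMS-arm women concealed disclosure, the variances and covariances are the same by symmetry and the signs reverse.

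**The case against.** The strongest reply is that little depends on the questionnaire. The main comparison of retention is an unadjusted intention-to-treat test, and adjustment is a conditional supplement. Subgroups are described as socio-demographic, and disclosure is not named as one of them. All of this stands, and it limits the reach of the point.

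Three stronger readings are tempting, and the protocol does not support them:

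- A reader might infer that the trial's principal result is biased. It is not, because that analysis uses no questionnaire item.
- A reader might infer that every soft item asked at baseline feeds the adjusted models. Social support and access costs are not in the listed baseline characteristics.
- A reader might infer that women who leave between allocation and interview would have no baseline data. Parity, marital status, education and age are collected for all screened women, and clinical data come from medical records. The article gives no interval between allocation and interview, so the extent of such loss, or any difference by arm, is unknown.

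The size is also open to challenge. The disclosure rate, retention gap and reporting shift have no source in the protocol, and the bias falls to zero with the shift. In the scenario worked through, it runs against the intervention and could not create a false claim of benefit.

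What the reply does not remove is the contradiction, or the fact that one of the two stated orders is poor practice in an open trial. This is not a detail that a journal article has left out: the article states the order twice, in opposite ways.

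**Conclusion.** The contradiction is certain, because it is on the face of the text. The bias is conditional: it needs sites to follow the Baseline section, answers to depend on the known arm, and an affected item to enter a model or subgroup. Under the illustrative assumptions the adjusted risk difference is off by about 1 to 3 points in either direction, roughly 9% (0.95/11) to 25% (2.76/11) of the 11-point target. The range shows order of magnitude and is not an estimate for this trial. Severity is moderate: the passages must be reconciled, but the unadjusted primary comparison stands whichever order was used.

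**What to change.** Correct the Baseline section to agree with Study population: the baseline questionnaire is completed before the sealed envelope is opened. Repeating the requirement in the section on randomisation and allocation would remove any doubt at the sites.

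For any woman already interviewed after allocation, use for adjustment and subgroups only items fixed before allocation or taken from screening or medical records. Since a regression model has one covariate set, in practice this means leaving reported disclosure out of the adjusted models if there are such women.

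The cost is a sentence and a change of order at the enrolment visit. The downside is a few interviews with women who are then not randomised. The change should be made early, because answers given after allocation cannot later be turned into baseline data.

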### Follow up

Follow up visits will occur at 6 and 24 months postpartum, at which time research assistant will administer the follow-up questionnaire. The follow up questionnaire will capture information on participants’ missed appointments, engagement with health workers and satisfaction with care, mobile phone access and using the WelTel intervention, and health related status/quality of life using the EuroQol 5-dimensional (EQ-5D) utility scores and twelve item short form survey (SF-12) standardized tools.

To investigate quality of life, we will first develop a patient generated index (PGI) to identify areas in the women’s lives that are affected by their HIV infection during pregnancy and nursing period; periods when the risk of transmitting HIV is high. A PGI is an individualized patient reported instrument that allows the respondent to state, weight and rate areas of importance to the patients’ lives that are affected by their illness. The PGI will also enable the investigators to assess the validity of the EQ5D and SF12 in this population and context.

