#### Secondary outcomes

Adherence to the WelTel SMS intervention measured as the proportion of women living with HIV who do not respond to the SMS within 7 days.Adherence to (i) ARVs measured as the proportion of women living with HIV who do not respond to the SMS within 7 days when suspected to be out of ARVs (i.e. failure to pick up ARVs that can cover her absence); (ii) facility-based delivery measured as the proportion of women who deliver in hospital; (iii) early infant HIV testing defined as the proportion of HIV-exposed infants who are tested for HIV within 8 weeks of birth measured as HIV –exposed infants with known HIV status at age 10weeks and (iii) exclusive breastfeeding defines as feeding the HIV-exposed infant only milk from the mother’s breast.Participant perceived facilitators and barriers of the WelTel SMS intervention (assessed as perceived reasons and challenges of use as well as suggestions to possible solutions).Cost compared with (i) effectiveness (levels of retention) from a payers’ perspective and (ii) quality of life (differences in pregnant women’s QALYs between the two trial arms.

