### Economic evaluation

We will perform an economic evaluation to assess WelTel SMS from a healthcare payer perspective. The primary outcome of the cost effective analysis (CEA) will be the incremental cost per additional mother-infant pairs that remain in PMTCT until infant is aged 24 months. A secondary outcome is averted infant HIV-infections at cessation of breastfeeding. For the cost-utility analysis the outcome will be quality adjusted life years (QALYs), based on responses to the SF-12 and EQ5D. For both analyses (CEA and CUA) we will report the incremental cost-effectiveness ratios (ICERs) that will be computed as the ratio of the incremental costs to provide WelTel SMS over usual care and incremental effects e.g. cost per additional mother-infant pairs that remain in PMTCT until infant is aged 24 months, cost averted infant HIV-infections at cessation of breastfeeding and cost per QALY.

A secondary analysis will also consider the incremental cost per averted deaths by bringing infants lost to follow up back and enabling treatment. Thus, we will determine ICER for cost per averted deaths. Deterministic sensitivity analysis will be to address uncertainty.

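### Pregnant women's QALYs are to be compared, but EQ-5D and SF-12 are scheduled only at 6 and 24 months postpartum, leaving no baseline or pregnancy utility

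*Protocol article*

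**What the plan says.** Under Secondary outcomes, the protocol article sets cost against "quality of life (differences in pregnant women’s QALYs between the two trial arms". Under Economic evaluation it names the source: "For the cost-utility analysis the outcome will be quality adjusted life years (QALYs), based on responses to the SF-12 and EQ5D".

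The Follow up section gives the schedule: "Follow up visits will occur at 6 and 24 months postpartum, at which time research assistant will administer the follow-up questionnaire". The content of that questionnaire includes health status or "quality of life using the EuroQol 5-dimensional (EQ-5D) utility scores and twelve item short form survey (SF-12) standardized tools". No other section schedules either instrument.

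The Baseline section lists what is asked at entry: socio-demographics, HIV diagnosis and ARV history, disclosure, then "HIV care and social support, mobile phone use as well as costs for accessing care". Costs are therefore recorded at entry, but no utility is. The baseline characteristics listed under Statistical methods contain no quality-of-life measure either.

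The Follow up section also describes a patient generated index covering pregnancy and nursing. It has no schedule. It is meant to identify affected areas of life and to help assess the validity of EQ-5D and SF-12, and it is not named as a source of QALYs.

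**The concern.** Women enter at the first antenatal visit, and the intervention starts then. A QALY is utility accumulated over time, so a QALY difference that includes pregnancy needs at least one utility from that period. Under this schedule the first utility comes after all of pregnancy and 6 months postpartum, when intervention women have been receiving weekly messages for months.

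Two things are lost. Any QALY total covering pregnancy would have to be extrapolated backwards from a measurement taken under treatment. And the adjustment for baseline imbalances that Statistical methods allows, if required, cannot be made for utility, although baseline utility is the natural covariate for a QALY comparison.

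A further question is who supplies the 24-month utility. It is collected at a visit at the same time point as the primary outcome, and the plan expects most control pairs to have left care by then.

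**Working it through.** **The plan's own figure.** The article gives no number for the QALY analysis. The only stated calculation is the sample size, checked here because its retention rates are used below. For 30% against 41%, two-sided 0.05 and 80% power, the standard two-proportion formula gives 296 per arm. Power is 80.5% at 300 per arm and 78.5% at 285 (300 less 5%). The stated 300 is reproduced closely enough and is not in dispute.

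**Unmeasured interval.** The article does not give gestational age at entry, so it is assumed to lie between 12 and 36 weeks of a 40-week pregnancy. It gives no QALY horizon either; enrolment to 24 months postpartum is borrowed from the definition of the primary outcome.

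- Months of pregnancy remaining = (40 − g)/52.18 × 12, where g is weeks at entry.
- Unmeasured share = (pregnancy months + 6)/(pregnancy months + 24).
- g = 12: 6.4 months; (6.4 + 6)/(6.4 + 24) = 12.4/30.4 = 41%.
- g = 20: 4.6 months; 10.6/28.6 = 37%.
- g = 36: 0.9 months; 6.9/24.9 = 28%.

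The only interval with a utility at both ends is 6 to 24 months postpartum, which is 18 months.

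**Cost of having no baseline utility.** For a single follow-up utility whose correlation with baseline is ρ, adjusting for baseline multiplies the variance of the arm comparison by about 1 − ρ². The article does not give ρ, so the gain is not quantified here. It is a gain in precision; under randomisation the unadjusted comparison is not biased by chance imbalance.

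**24-month utilities, conditional on only retained pairs being interviewed.** Inputs from the Sample size section: 30% retained in control, an 11-point difference (so 41% with intervention), 300 per arm.

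- Control: 300 × 0.30 = 90 observed, 210 missing (70%).
- Intervention: 300 × 0.41 = 123 observed, 177 missing (59%).
- Total observed: 90 + 123 = 213 of 600, so 64.5% missing.
- Detectable standardised difference at 80% power: (1.96 + 0.84) × √(1/90 + 1/123) ≈ 0.39.

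**The same, if all women are sought and only the stated 5% withdraw.** 300 × 0.05 = 15 missing and 285 observed per arm. The detectable standardised difference is (1.96 + 0.84) × √(2/285) ≈ 0.23.

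**The case against.** The strongest reply is that the phrase about pregnant women may simply name the enrolled population rather than the measurement window. The article states no QALY horizon and no area-under-the-curve method, and a QALY difference over the postpartum period can be computed from the two scheduled measurements. That stands. A reader might infer that the cost-utility analysis cannot be done at all; the article does not support this. Even on the population reading, though, there is no baseline utility and nothing is measured before 6 months postpartum.

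A reader might also infer that missing utilities will follow the primary outcome. The article does not say so. The Sample size section separates 5% withdrawal from the study from non-retention in care, willingness to be followed to 24 months is an inclusion criterion, and the Follow up section does not limit interviews to retained pairs. The 70% and 59% are therefore one conditional case, and missingness at 6 months would depend on earlier attendance. What remains is that no route to women who have left care is described. The tracing in the Intervention section is set off by an unanswered SMS, which control women do not receive, so it cannot be relied on to reach both arms equally.

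A third tempting reading is that chance imbalance in baseline utility would bias the result. Under randomisation it costs precision.

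Finally, a journal article condenses, and the regression model and handling of missing data properly belong to an analysis plan that is not shown. Their absence is not criticised here. The instrument schedule and baseline content are different, because the article sets them out and the utility measure is not among them.

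**Conclusion.** The point holds as a gap between a named outcome and the data scheduled to support it. Followed as written, the plan yields no utility during pregnancy or at baseline. The unmeasured part is about 28% to 41% of the period from enrolment to 24 months postpartum, given entry at 36 to 12 weeks and that horizon, both assumed. QALYs over pregnancy cannot be anchored, and the comparison loses the precision that baseline adjustment would give.

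The loss of 24-month utilities is a secondary risk that depends on how interviews are organised. At the two extremes, 213 or 570 of 600 women would supply one. The first is the retained-only case; the second is 285 × 2, with withdrawal alone.

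The trial's primary outcome and the primary economic outcome, cost per additional retained pair, are unaffected. The change is worth making because it is cheap, but it concerns one part of one secondary objective.

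**What to change.** 1. Add EQ-5D and SF-12 to the baseline questionnaire.
2. Give that questionnaire before randomisation. The Study population section requires its completion before randomisation, while the Baseline section places it after recruitment and allocation. The two must be reconciled, because a utility reported once the arm is known is not a clean baseline.
3. Adjust the QALY comparison for baseline utility, and state the period over which QALYs are counted.
4. For women already enrolled without a baseline value, restrict the QALY outcome to the postpartum period or report the limitation. Only 6 to 24 months is bracketed by measurements.
5. State that the 6- and 24-month questionnaires will be sought from all randomised women regardless of retention in care. Phone contact is feasible because phone access is an inclusion criterion, but phones may be shared and a trusted contact may read messages, so confidentiality safeguards are needed. The Recruitment section describes registering numbers only for the intervention arm, so contact details are needed for control women too.

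The cost is a few minutes per baseline interview and some extra contact effort at 6 and 24 months.
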